## Abstract

**Introduction:**

Despite improvements in health outcomes for children, early childhood dental caries (ECC) remains a chronic lifestyle-mediated disease that affects an estimated 600 million children worldwide. Parental influence on oral health-promoting behaviours is pivotal in preventing ECC. The latest WHO publications *Ending Early Childhood Dental Caries* and *Mobile Technologies for Oral Health* highlights the opportunity for mobile Health programs (including text message programs) to improve oral health behaviours and oral health self-efficacy. In response, our team of parents, oral health professionals (academics and health promotion experts), and IT specialists co-designed a 12-week, behavioural theory-informed text message program (called *SmilesUp*) to address behavioural risk factors specific to ECC. This randomised trial aims to assess whether the *SmilesUp* program improves parents’ oral health promoting behaviours (like tooth brushing twice a day with toothpaste) and oral health self-efficacy for their children compared to usual care.

**Methods and analysis:**

A randomised controlled trial with a 1:1 parallel design will be conducted among 150 parents with children diagnosed with ECC and accessing public dental care in NSW, Australia. Patients will be stratified by hospital site, and modality of care (Dental General Anaesthetic (DGA) or not) and then randomly assigned to either immediately receive the SMILESup text messaging intervention or receive the program at the end of the study period. The primary outcome at 12 weeks is twice daily brushing with fluoride toothpaste. Secondary outcomes include changes in the intake frequency of sugared drinks and foods, oral health promoting bedtime routines and oral health self-efficacy. The primary analysis will follow an intention-to-treat principle. In addition, a process evaluation will examine barriers, enablers, and opportunities to scale the program.

**Ethics and dissemination:**

Ethics approval has been obtained from the Western Sydney Local Health District Human Research Ethics Committee 2022/ETH01920. Study results will be disseminated via peer-reviewed publications and presentations at conferences.

**Trial registration:**

**Trial registration number**: This clinical trial has been prospectively registered on the ANZCTR from the 27^th^ of March 2023. Registration number: ACTRN12623000325606.

## Introduction

Early childhood caries (ECC) remains a complex childhood problem that affects more than 600 million children worldwide [1]. It is defined as “the presence of one or more decayed (non-cavitated or cavitated lesions), missing (due to caries), or filled tooth surfaces in any primary tooth in a child under the age of six” [2]. Although dental caries is preventable, young children continue to require invasive procedures provided under dental general anaesthetics (DGA) to treat ECC [3–5]. In Australia, and New South Wales (NSW), these admissions affect one in every 250 children with a repeat admission rate of 9% within two years and a further 9.8% admission rate for subsequent children in the same family [6]. The repeat admissions also present a significant cost to individual families and the health care system [3]. Developing innovative programs that enhance parents’ daily oral health practices for their child is crucial for preventing the progression of ECC and reduce both disease recurrence and related hospital admissions [7–9]. As a non-communicable lifestyle-associated disease ECC is preventable through good oral hygiene, tooth brushing with toothpaste, diets low in free sugars and oral health promoting bedtime routines that omit milk feeding throughout the night [1,10]. The latest American Academy of Paediatric Dentistry’s policy on ECC prevention highlights the need to reduce sugar-containing foods and drinks and adopt early oral hygiene measures including twice daily brushing [11]. A recent prospective study has also shown that for children two and three of age, brushing less than twice a day would double the likelihood of future caries incidence at age five [12]. The World Health Organisation’s (WHO) latest report on *Ending Early Childhood Dental Caries* highlights the crucial role of parental knowledge, motivation and capability (i.e. oral health self-efficacy) for oral health promoting behaviours on the dental outcomes of their children [9].

New approaches for ECC disease management must consider the strategic directions provided by the WHO’s Global Health Action Plan (2023–2030) and consider the use of mobile technologies [7,13]. The WHO’s *Mobile technologies for oral health* guideline highlights using mobile health interventions as a scalable and impactful “best-buy” intervention to increase oral health literacy and improve oral health behaviours [7,9]. It defines mobile Oral Health (mOralHealth) as the use of mobile and wireless technologies (such as mobile phones and text messaging programs) to support the achievement of oral health objectives and highlights its use to complement the provision of basic clinical oral health care [14]. When applied to preventing ECC, mHealth programs can complement clinical care by providing parents and carers (referred to as parents in this paper) with additional knowledge, and positive reinforcements through messages with links to video demonstrations accessed in the home contexts where oral health habits are being formed. This type of intervention is synergistic with the WHO’s definition of health literacy which recognises the broader cognitive and social skills that determine the motivation and ability of individuals to gain access to, and understand information in ways that promote good health [15,16]. Therefore, the outcome measures for this study, although primarily behavioural will also include measures for the construct of oral health self-efficacy.

Text messaging programs, co-designed with consumers and health professionals are an effective, equitable and cost-effective solution to support behaviour change and prevent a range of non-communicable diseases [17–19]. Most emerging mHealth research addressing oral health, targets behaviour change in high-risk populations [20] by focusing a single behaviour, whether it be on oral hygiene behaviours [21], night-time routines [22] or diet [23]. A comprehensive program to address a range of lifestyle risk behaviours specific to the prevention and management of ECC has not been created in the Australian context. Specifically, a recent Australian review identified a gap and a need to co-design mHealth programs specific for parents of children 0–6 years old who have ECC [24].

In response, our team has worked with parents and a range of health professionals to co-design a text messaging program (*SmilesUp*) to support ECC prevention in the NSW public dental service context. *SmilesUp* contains 36 positively framed oral health messages assessed to be useful, readable and acceptable by consumers accessing NSW public dental services [25]. This study aimed to test the effectiveness of the *SmilesUp* intervention on oral health behavioural outcomes and self-efficacy.

## Materials and methods

### Study aim

This study aimed to test the effectiveness of the *SmilesUp* text message program to change oral health behaviours and self-efficacy of parents in a single-blinded randomised controlled trial, compared to usual care. We will also conduct a process evaluation to assess barriers and enablers of the program to inform future scale-up plans.

### Study design

The SMILESup study is a multi-site, single-blinded (dental practitioner blinded, patient unblinded), parallel designed randomised controlled trial of 150 parents (who have children 0–6 years old inclusive with a ECC diagnosis), testing the effectiveness of a 12-week co-designed text message program (*SmilesUp*) to support oral health behaviour change in their children and parental self-efficacy compared to usual care. The intervention participants (n = 75) will receive the program after randomisation and the control group (n = 75) will receive the program after the 12-week trial period. Fig 1 shows our SPIRIT schedule of enrolment, interventions, and assessments. Fig 2 shows the CONsolidated Standards of Reporting Trials (CONSORT) RCT study flow.

**Fig 1 pone.0310561.g001:**
[figure not shown]
SPIRIT Schedule of enrolment, intervention, and assessments.

**Fig 2 pone.0310561.g002:**
[figure not shown]
SMILESup CONSORT RCT study flow chart.

### Setting

The study population will consist of parents with children diagnosed with ECC who are either awaiting or receiving dental treatment, including but not limited to DGA within the NSW public dental service, in Australia. This intervention will run alongside and be an adjunctive support tool for parents whilst their children are in a clinical course of care within the public dental service system. Children in both groups will receive appropriate clinical and preventive care, governed by the existing policies within NSW public dental services [26,27]. Specifically, this trial will take place in six local health districts across metropolitan, rural and regional areas. These community dental clinics all refer to the two tertiary paediatric dental departments within NSW Health. These clinics predominantly provide a fee-free safety-net dental service for families who cannot afford private dental care.

### Patient population

Previous studies in Australia have indicated that this population group accessing public dental care has the highest severity of disease [6] and lower uptake of oral health promoting behaviours and low oral health literacy levels [28]. A recent study showed that only 53% of this population performed the recommended oral health behaviours (tooth brushing twice a day with toothpaste) to prevent ECC for their children [29].

### Sample size

A sample size of 150 will enable the detection of a 25% difference between intervention and control groups with an 80% power. The clinically meaningful impact of the intervention was chosen with a health equity lens. A recent cross-sectional study of a similar Australian population group from lower socioeconomic areas accessing public dental services reported that 53% of children between 3–8 years old brush twice a day with toothpaste [29]. However, 78% of children in Australia from high-income families brush twice a day with toothpaste [30]. Thus, to determine a clinically meaningful difference we aimed to increase the number of families brushing twice a day with toothpaste from 53% of the population to be comparable to the 78% of children from high-income households who were achieving the target behaviour. This required an increase of 25%. Therefore, a sample size of approximately 150 will achieve an 80% power, to observe a meaningful difference of a 25% increase of participants who brush twice a day with toothpaste in the intervention compared to the control group at three months (53% to 78%), using a 5% level of significance and accounting for a 25% drop-out rate.

### Participant eligibility

Inclusion criteria are parents of children who have all the following:

diagnosis of dental caries (tooth decay)age 0 to 6 years inclusivewaiting (or have attended) a public dental service for dental caries (tooth decay) within the public health system in NSW.

Parents will be excluded if they:

are already participating in a text message-based study on lifestyle risk factors for health.have insufficient English skills to provide informed consent or read and understand text messagesare unable to comply with study requirements.

Parents of these children must also own an operational mobile phone capable of sending and receiving SMS text messages; and provide written informed consent.

### Recruitment and consent

Recruitment will be performed around existing clinical workflows within clinical settings in NSW public dental services. Researchers will screen parents for eligibility. Only parents of children who fit the eligibility criteria will be invited to take part in the study. These parents will be provided with a recruitment information flyer. The recruitment information flyer will contain a QR code to a Research Electronic Data Capture (REDCap) link with an Expression of Interest form and a further link to the Participant Information Consent Forms (PICF). The PICF visible via the REDCap link will contain an eConsent form that will also be held and stored securely on REDCap. Parents will have access to the PICF and be able to discuss involvement with the rest of their families and contact researchers with further questions before providing consent. Parents will also be able to take the flyer home before deciding to enrol, and the contact details of the researcher will be available in case any potential participant has further questions to enable informed consent. For consent to be obtained, the parent must complete and sign the eConsent before any data collection or intervention delivery occurs. At the parents request, paper versions of the PICF and enrolment forms will be available. The lead researcher may delegate and train available clinicians/researchers at the study sites to explain the study and answer more questions in detail.

### Randomisation and blinding

Randomisation will also occur after consent and baseline data collection. Participants will be randomly assigned to either the control or the intervention group with a 1:1 allocation ratio, stratified by recruitment site (community dental clinics vs. tertiary paediatric settings) and modality of care (DGA vs. non-DGA). Randomisation will be generated by the study statistician using the Randomise R library of R statistical software (V.4.3.2) and is based on both permuted block sizes and stratification, where stratification occurs by site (community dental clinics vs. tertiary paediatric settings) and the modality of care (DGA vs. non-DGA) only. The intervention allocation sequence will be incorporated into REDCap so that researchers recruiting and analysing the data will be blinded to treatment allocation. Participants will be notified of their treatment allocation via text message the following Monday after enrolment, thus participants will not be blinded to allocation. As the intervention is low risk and participants can opt-out, it is anticipated that emergency unblinding will not be necessary for this study.

### Intervention—The *SmilesUp* 12-week text messaging program

The *SmilesUp* text message program will deliver 36 messages over 12 weeks using a pre-programmed delivery algorithm informed by consumer engagement. We have used a co-design process that has been previously published [31], driven by behavioural theory to be synergistic with the principles in the current WHO guidelines [17,32]. These principles highlight the importance of co-designing and adapting mHealth programs for specific local contexts and target populations. By co-designing the program, we first identified that parents were seeking reminders, reassurance, and video resources from health professionals that they could access on their smartphones at home to complement the clinical care and advice they had previously received. Consumers and clinicians were also consulted about the length of the program and provided with evidence for the time taken for effective behaviour change [31,33,34]. The final pre-programmed delivery algorithm, developed with consumer input is hosted on the TextCare™ platform. The TextCare™ platform is a proprietary and custom-built platform that has been successfully used to address lifestyle behaviour change for the management of a range of cardiometabolic diseases [35,36]. The program is semi-personalised to include their child’s name in some messages and allows the parents to choose when they receive the messages based on the information provided by parents when they sign up for the study.

### Intervention development, patient, and public involvement

Intervention development occurred in a separate phase of the project before the commencement of the RCT [31]. It involved consultation at the inception of the program, with end users, namely parents accessing NSW public dental services. Our intervention development was uniquely co-designed with parent consumers (n = 20) and a wide range of health professionals (n = 17) including paediatric specialists, general dental practitioners, health promotion, health policy professionals, IT application specialists, researchers, oral health dieticians and academics working within the NSW public dental services. This process is described in more detail in a previously published conference paper [31].

A summary of the three main steps for our patient and public involvement, during the co-design process are as follows. Firstly, the parent groups were consulted to identify target behaviours barriers and enablers related to oral health promoting behaviours related to ECC.

The primary target behaviours identified included:

Brushing twice daily with toothpaste

Other secondary target behaviours included:

Reducing the consumption of sugar-sweetened beveragesReducing the frequency of a child going to bed with milk in a bottle.Reducing the consumption of sugary foodsIncreasing the regular consumption of water

Secondly, the group agreed to the program aims developed using the WHO mOral Health Literacy framework shown in Table 1. Additionally, interested parents and health professionals had the opportunity to draft text message content. Thirdly, a broader group of consumers and health professionals working with the target group assessed the acceptability and usefulness of the draft messages [25]. Only messages that had high acceptability and usefulness by parents and health professionals were included in the final set. The high-level sequence of the final 36 messages and examples of some messages are shown in Figs 3 and 4. Each of the final messages was mapped to the target behaviours, barriers and enablers identified by the parents and linked to a specific behaviour change techniques [31].

**Fig 3 pone.0310561.g003:**
[figure not shown]
Intervention component and sequence.

**Fig 4 pone.0310561.g004:**
[figure not shown]
Examples of text messages.

**Table 1 pone.0310561.t001:** SMILESup program aims to use the WHO moral health literacy module framework.

**Aim**	To improve the oral health behaviours and oral health self-efficacy of parents and their children with ECC.
**Implementers**	Partnership between dental practitioner and specialist within local health districts, public health professionals and academics.
**Target audience/groups**	Parents are intermediaries to reach their children aged 0–6 years old who are waiting for a dental treatment including dental care with DGA.
**Potential technologies**	Semi-personalised SMS, other media assets including URL links to video resources provided by text message.
**Primary outcomes**	Primary outcome health behaviour: Brushing twice a day with toothpaste–increase of 25% from baseline brushing levels.
**Secondary outcomes**	Secondary outcome 1) Oral health behaviours: • Use of fluoride toothpaste • Sugary food and drink consumption • Oral health promoting night-time routines • Water consumption 2) Oral health self-efficacy
**Impacts**	Short-term: effective oral health habit formation to ensure the sustainability of prevention and the self-management of ECC. Longer-term clinical outcomes: reduced decay and the need to have a repeat general anaesthetic appointment for ECC.

### Intervention group

The intervention group will receive the *SmilesUp* text message support program in addition to the usual clinical care and advice provided in the clinical setting. Participants will be informed that this is primarily a one-way messaging service and will receive their semi-personalised messages at the specific time of the day they have chosen at the beginning of the intervention.

At the end of the 12-week program, parents will be asked to fill in a standardised questionnaire to measure the change in oral health behaviours and oral health self-efficacy. On completion, parents will also have the option to attend focus groups or semi-structured interviews to provide more in-depth feedback.

### Control group

The control group will receive usual care, which consists of oral hygiene instruction and dietary advice provided in the clinical setting. The control group will enrol in the *SMILESup* study which includes completing a standardised questionnaire that records general demographic questions, baseline oral health behaviours, and self-efficacy. At the end of the 12 weeks, they will be required to complete a similar standardised post-survey questionnaire about their oral health behaviours, and self-efficacy. Upon completion of the post-survey, the control group parents will be offered the *SmilesUp* text message program.

### Data collection & study outcome measures

Data will be collected from participants at baseline and follow-up (3 months post-allocation). We developed a self-reported questionnaire to measure all behavioural and self-efficacy outcomes pre- and post-intervention available in our protocol. A summary of our outcomes is shown in Table 2 and Fig 1. Data collection for baseline and post-intervention will primarily be collected electronically using REDCap. However, parents also have the option of providing their details so that the research team can contact them or provide them with the opportunity to complete the enrolment process or post-intervention data collection at home in their own time. Where requested, hard copies of these questionnaires will also be made available.

**Table 2 pone.0310561.t002:** Study outcomes.

Outcome	Assessment measure
*Primary outcome*:	
**Tooth brushing for their child twice a day with toothpaste**	Self-reported questionnaire adapted from existing questions used to evaluate other NSW Health programs [37].
*Secondary outcomes*:	
**Fluoride toothpaste use**	Self-reported questionnaire adapted from existing questions used to evaluate other NSW Health programs [37].
**Sugary drinks consumption to Australian guidelines**	Self-reported questionnaire from cut-offs determined by current Australian guidelines [38] and adapted from existing questions used to evaluate other NSW Health programs [37].
**Sugary foods consumption to WHO guidelines**	Self-reported questionnaire from recommendations by the WHO guidelines on the consumption of sugars for the prevention of ECC [39] and adapted from existing questions used to evaluate other NSW Health programs [37].
**Water consumption**	Self-reported questionnaire adapted from existing questions used to evaluate other NSW Health programs [37].
**Bedtime routines (milk before or during sleep)**	Self-reported questionnaire adapted from existing questions used to evaluate other NSW Health programs [37].
**Oral health self-efficacy**	Self-reported questionnaire adapted from previous literature using the COM-B framework to measure Oral Health self-efficacy [40].

### Primary study outcome: Tooth brushing

The primary outcome is based on whether the parents adhered to the current recommended guideline and brushed their child’s teeth twice a day with toothpaste [11]. This item will be analysed as a binary (*yes/no*) response to the question adapted from an existing question used to evaluate other NSW Health programs [37] “How often do you brush your child’s teeth with toothpaste?” A *yes* response will be considered for patients answering, “Twice a day” or “More than twice a day” and a *no* response to those answering, “Once a day”, “few times a week”, or “Don’t know /unsure”.

### Secondary outcomes

Secondary behavioural outcomes will be analysed as a binary (*yes/no*) response to behavioural questions that have been adapted from existing questions used to evaluate other NSW Health programs [37]. These include:

*Type of toothpaste used*. This secondary behavioural outcome considers whether a parent is using fluoride toothpaste according to current guidelines [9]. This will be calculated based on the response to the question: “What type of toothpaste do you put on our child’s toothbrush?” [37]. A *yes* response will be considered for “Children’s fluoride toothpaste”, “Standard fluoride toothpaste” or, “Prescribed toothpaste” and a *no* response to those answering, “Non-fluoride toothpaste” and “Don’t know/unsure.”*Frequency of sugared beverage consumption for the child*. This secondary behavioural outcome considers the number of sweet beverages a child has per week based on cut-offs determined by current Australian guidelines [38]. This will be calculated based on the response to the question “How often does your child drink sugar-sweetened drinks (such as soft drinks, cordials, sports drinks, flavoured milk, fruit juices, energy drinks or iced teas?)” A *yes* response will be considered for “Rarely” or “Never” and a *no* response for those answering, “Every day” “A few times a week” and “Don’t know/unsure.”*Frequency of sweet food consumption for the child*. This secondary behavioural outcome considers the dietary behaviours of the child related to the frequency of sweet foods per week based on recommendations from the WHO guidelines for the consumption of sugar [39]. This will be calculated based on the response to the question “How often does your child eat sweet foods like chocolates, sweetened cereal, ice cream, flavoured milk or yoghurt, biscuits, cakes, pastries, or snack/muesli bars?” A *yes* response will be considered for “Rarely” or “Never” and a *no* response for those answering, “Every day” “A few times a week” and “Don’t know/unsure.”*Bedtime routines related to the frequency and timing of milk consumption at night*. This secondary behavioural outcome measure considers the specific risk behaviour of consuming milk before or during sleeping hours as outlined in the WHO’s ECC report [9]. This will be calculated based on the response to the question “How often does your child go to bed with milk in a sippy cup or bottle?” A *yes* response will be considered for “Rarely” or “Never” and a *no* response for those answering, “Every day” “A few times a week” and “Don’t know/unsure.”*Frequency of water consumption*. This secondary behavioural outcome measures the positive behaviour of frequently consuming water. This will be calculated based on the response to the question “How often does your child drink water?” A *yes* response will be considered for “Every day” and a *no* response for those answering, “A few times a week” “Don’t know/unsure” “Rarely” or “Never.”*Oral Health self-efficacy*. To provide some information on the construct of oral health self-efficacy, we will collect a standardised set of six questions on each of the three target behaviours (oral hygiene, diet and bedtime routines) that were adapted from previously published literature [40]. The six questions consider capability (physical capability and psychological i.e. knowledge capability), opportunity (physical opportunity, social opportunity), and motivation (reflective motivation, and automatic motivation) [40,41]. These questions draw upon the COM-B framework which itself draws upon the Health Beliefs Model (HBM) and the Theory of Planned Behaviour (TPB) [42,43]. The total oral health self-efficacy measure for each target behaviour (oral hygiene, diet and bedtime routines) will be analysed by a composite measure out of 60. Secondary analysis for each question includes a binary measure which will be dichotomously categorised where a score of 8 or more on a 10-point Likert scale is considered a *yes* and a score below 8 is considered *no*.

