
### Statistical analysis

Our statistical analysis will follow an intention-to-treat principle. A full pre-specified statistical analysis plan will be developed and finalised before study completion, data lock and analysis. Normally distributed continuous variables will be expressed as means with standard deviations. Non-normally distributed variables will be expressed as medians and interquartile ranges. Binary variables will be presented as proportions with their 95% confidence intervals (CI). The proportion of parents who meet the primary outcome of toothbrushing twice a day with toothpaste at baseline and 3 months will be presented descriptively by treatment groups. An odds ratio of brushing their child’s teeth twice a day with toothpaste at 3 months comparing treatment vs. control (reference group) will be estimated with a 95% CI using a logistic regression model adjusting for whether parents are toothbrushing twice a day with toothpaste at baseline and stratification variables. All dichotomous secondary outcomes will be analysed using the same logistic regression model and continuous secondary outcomes will be analysed using linear regression. A statistical significance level of 0.05 will be used. Interaction between treatment and pre-specified covariates will be conducted to explore the heterogeneity of our results. Sub-group analyses will be conducted for treatment modality (DGA vs. non-DGA), and site (tertiary vs. non-tertiary). No multiplicity adjustments will be performed for secondary outcomes as they are exploratory by nature. We will not be conducting further interim analyses with stopping guidelines. All analysis will be undertaken using R.

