All data for this study will be collected from the individuals themselves. No additional data will be gathered from medical/ health records. Following the NHMRC guidelines on the management of data and information in research, paper and electronic study information, including the consent forms and questionnaires, will be securely stored until 5 years after the completion of the study. Electronic data will be permanently deleted from servers and hard copy documentation shredded and disposed of in secure confidential bins provided by hospital sites. The destruction of the data will follow processes following the University of Sydney Research Data Management processes in alignment with the NHMRC guidelines.

For the process evaluation, where Zoom or online telephone links are sent, meetings will be password protected. Further confirmation of the receipt of the PICF will be provided on the recordings. All data from the recordings will be stored on a secure encrypted server of the University of Sydney’s Research Data Store and deleted from any device. Any quantitative metrics to assess fidelity will be analysed by R [45] or SPSS v22. All qualitative data will be analysed using NVivo version 12.0 [46] coded data will be analysed in themes qualitative methodologies, following a framework analysis approach [47].

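### Scoring an unsure answer as not using fluoride toothpaste can turn a gain in knowledge into an apparent change in behaviour, in favour of the programme

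*Protocol article*

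**What the plan says.** Under Secondary outcomes, the toothpaste item is introduced as a measure of behaviour: "This secondary behavioural outcome considers whether a parent is using fluoride toothpaste according to current guidelines". Three answers naming a fluoride or prescribed paste count as yes. The no category is made up of parents "answering, “Non-fluoride toothpaste” and “Don’t know/unsure".

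Table 1 lists "Use of fluoride toothpaste" under oral health behaviours. The Introduction says mobile health programmes of this kind complement clinical care "by providing parents and carers (referred to as parents in this paper) with additional knowledge".

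The answers are self-reported. The Data management plan states that "All data for this study will be collected from the individuals themselves", and Randomisation and blinding says of the parents that "thus participants will not be blinded to allocation". No check of the product in the home is described.

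On analysis, the Statistical analysis section says "All dichotomous secondary outcomes will be analysed using the same logistic regression model", that is, the primary-outcome model adjusted for the baseline value and the stratification variables.

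**The concern.** The no category mixes two kinds of parent: those who use non-fluoride paste, and those who do not know what they use. Some of the second kind already use fluoride. For them, learning what is in the tube is enough to change the recorded outcome, with no change in what goes on the brush.

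The control group receives the programme only after the 12-week questionnaire, so this misclassification can shrink more in the intervention arm than in the control arm. Counting an unsure answer as failure usually looks conservative. Here it can favour the intervention.

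Baseline adjustment does not remove the problem, because the baseline no is the same mixture of non-users and unsure users.

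The other behavioural items also score unsure as no. They ask how often something happens, which a parent can observe. This item asks about the composition of a product, which a parent may simply not know.

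At stake is the reading of one listed behavioural outcome. The Conclusion says the behavioural and self-efficacy outcomes will provide initial evidence for expanding the programme.

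**Working it through.** **Analysed sample.** The Sample size section gives 53% vs 78%, 80% power, a 5% level and 25% drop-out. With a two-sided test, pooled variance and no continuity correction, n = [1.96·√(2·0.655·0.345) + 0.842·√(0.53·0.47 + 0.78·0.22)]² / 0.25² = 55.6, so 56 per arm. Then 56/0.75 = 74.7, so 75 per arm and 150 in total. The stated N reproduces. It concerns the primary outcome; I use it only to take 56 analysed per arm.

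**Assumptions (none of these figures is in the documents).**
- u: share of control parents answering unsure at 12 weeks.
- f: share of unsure parents whose paste already contains fluoride.
- r: extra share of unsure parents in the intervention arm who come to know what they use.
- Among parents who know, 80% use fluoride paste.
- True use is the same in both arms, so the real effect is zero.

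**Formulas.**
- Coded yes, control = 0.80·(1 − u)
- Coded yes, intervention = 0.80·(1 − u) + u·f·r
- Spurious difference = u·f·r
- Chance of p<0.05: two-sided, unadjusted test of two proportions, 56 per arm

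| u | f | r | Control | Intervention | Difference (points) | Odds ratio | Chance of p<0.05 |
|---|---|---|---|---|---|---|---|
| 5% | 50% | 25% | 76.0% | 76.6% | 0.6 | 1.04 | 5.1% |
| 10% | 80% | 25% | 72% | 74% | 2 | 1.11 | 5.6% |
| 20% | 80% | 25% | 64% | 68% | 4 | 1.20 | 7.3% |
| 10% | 80% | 75% | 72% | 78% | 6 | 1.38 | 11% |
| 20% | 80% | 50% | 64% | 72% | 8 | 1.45 | 15% |
| 20% | 80% | 75% | 64% | 76% | 12 | 1.78 | 28% |
| 30% | 80% | 75% | 56% | 74% | 18 | 2.24 | 52% |

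Where f = 80%, true use is 80% in both arms. In the first row it is 0.76 + 0.05·0.50 = 78.5% in both. If every unsure intervention parent found out (u = 30%, f = 80%, r = 100%), the difference would be 24 points; I treat that as an extreme.

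**What a three-category report would show.** Take the row u = 20%, f = 80%, r = 75%. The unsure share is 20% in control and 20%·(1 − 0.75) = 5% in intervention.
- Protocol coding (unsure = no): 64% vs 76%, +12 points.
- Parents who know only: 64/80 = 80% vs 76/95 = 80%, no difference.
- Unsure = yes: 84% vs 81%, −3 points.

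The artefact vanishes among parents who know, and the two bounds lie on either side of zero.

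This analysis is not assumption-free. With u = 20%, f = 50%, r = 50%, restricting to parents who know gives 64/80 = 80% vs 69/90 = 76.7%, a deficit of 3.3 points although true use is 74% in both arms. That is why the bounds belong beside it.

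**The case against.** **The teaching effect is not shown.** Table 1 lists fluoride toothpaste use as an outcome. The target behaviours under Intervention development are twice-daily brushing with toothpaste, sugary drinks, milk in a bottle at bedtime, sugary foods and water. Toothpaste type is not among them, and the final messages were mapped to those targets. The Introduction's remark on knowledge describes mobile health programmes in general, and the message examples are in figures not shown. This stands: a reader might infer that the programme targets fluoride recognition and so will cut unsure answers, but the text does not support that.

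**Knowledge can rise in both arms.** Controls receive oral hygiene instruction and dietary advice in clinic, and both arms answer the toothpaste question at baseline, which may itself prompt a look at the tube. This also stands. Only the difference between arms matters, and its size is unknown.

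**The larger figures depend on the assumptions.** The 11%, 28% and 52% all assume a 75% fall in unsure answers. A fall of a quarter gives 2 to 4 points and 5.6% to 7.3%. It would therefore be wrong to state flatly that the estimate is biased or that the false-positive rate is materially above 5%.

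**The rule is pre-specified and defensible.** Unsure is scored as no for the primary outcome and the behavioural items alike, and one may choose to count only parents who can report fluoride use. That is reasonable for an outcome called known use. It fits less well with one described as whether the parent is using the product.

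**The stakes are modest, and the analysis plan may add a sensitivity analysis.** Both are true. The coding and the behavioural label are nonetheless fixed in this document, and the exploratory label is given as the reason for not adjusting for multiplicity; it does not cure measurement error that differs by arm.

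**Conclusion.** The concern holds as a possible bias of unknown size, in a direction that favours the programme. It rests on the stated coding, on the timing of the messages relative to the 12-week questionnaire, and on the condition that the messages help parents recognise fluoride in a toothpaste they already use. Under the assumed rates the spurious difference is from under 1 point to about 18 points, with a chance of p<0.05 from about 5% to 52% at 56 per arm when nothing about behaviour differs. The lower part of that range is negligible, and the documents cannot say where in it the trial lies.

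It concerns one secondary, exploratory outcome. The primary outcome, brushing frequency with toothpaste, is not touched. The point merits a small change before data lock but does not justify replacing the pre-specified coding.

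**What to change.** Keep the coding as written and add three things before data lock.

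1. Report fluoride, non-fluoride and unsure answers by arm at baseline and 12 weeks.
2. Add a sensitivity analysis that does not count unsure as non-use: for example, fluoride vs non-fluoride among parents who know, with bounds that set all unsure answers to yes or all to no.
3. State in advance that no behaviour change will be claimed if the effect comes only from fewer unsure answers. Otherwise, rename the outcome reported known use of fluoride toothpaste.

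Imputing unsure answers from baseline toothpaste type is not recommended as the main analysis. Unsure is an observed answer, and for parents unsure at both times imputation rests on an untestable assumption.

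The cost is one table and one extra analysis, using answers the questionnaire already records, and a possibly less favourable conclusion for this outcome.
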